## Abstract

**Background:**

The lockdown associated with the COVID-19 pandemic is likely to impact people’s mental health, especially those from economically disadvantaged and vulnerable sections of society. Mental health can be affected by many factors, including fear of disease transmission, from response measures against the pandemic like social distancing, movement restriction, fear of being in quarantine, loneliness, depression due to isolation, fear of losing work and livelihood and avoiding health care due to fear of being infected. Telephonic befriending intervention by non-specialists will be used to provide social and emotional support to the youth from the Deen Dayal Upadhyaya Grameen Kaushalya Yojana (DDUGKY), an initiative of the Government of India. This study aims to promote mental wellbeing and reduce depressive symptoms by assisting participants to mobilise social support from family, friends and significant others by using the telephonic befriending intervention.

**Methods:**

In this article, we report the design and protocol of a multi-centre cluster randomised controlled trial. In total, 1440 participants aged 18–35 years who have recently completed their course out of the DDU-GKY initiative will be recruited in the study from 12 project-implementing agencies (PIAs) across six geographical zones of India. Participants from 6 of these agencies will be assigned to the telephonic befriending intervention arm, and the other six agency participants will be assigned to the general enquiry phone call arm (control). The primary outcomes of this study are mental wellbeing, depressive symptoms and perceived social support. Baseline assessments and follow-up assessments will be carried out 1 month following the intervention using WHO-5, PHQ and MSPSS-12 questionnaires. The befriending intervention will be provided by DDU-GKY staff, whom a virtual training programme will train.

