In an epidemic outbreak, psychosocial interventions are essential [26] and social support has been shown to have a direct relationship with positive mental health and acts as a buffer against various stressors affecting mental health [27]. People with strong social relationships enjoy a sense of security and belonging to a network of systems that acts as a protective factor against various mental health issues [28].

Befriending is most often delivered by lay personnel or non-specialist workers, and [29] it is found that their use in the care of people with common mental disorders was cost-effective and cost-saving. In our trial, the intervention will be provided by DDU-GKY staff, which will enhance the existing staff, reduce cost, improve sustainability as the staff will be empowered to identify similar mental health issues in students in the future and increase acceptability as the staff are always available. Before the main trial, we plan a pilot trial among the students of the PIA at Rajagiri University, Kerala. Following the pilot trial, Rajagiri University team will lead the trial across 28 states of India, with the support of the Ministry of Rural Development. This nationwide telephonic befriending intervention is set out to address immediate priorities and strategies for providing emotional and practical support to the vulnerable people, in the context of COVID-19-related lockdown. We hypothesise that participants, whom we offer emotional, social and practical support through befriending, will experience lesser symptoms of depression and have better mental health compared to participants who do not receive this intervention.

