## Methods

### Aim

The overall aim of the ReaCH intervention trial is to test the effectiveness of the befriending intervention among young adults in reducing mental health issues like anxiety, depression or suicidal behaviour in the context of the COVID-19 pandemic and the related restrictions. The befriending intervention will be used to determine if it can promote mental wellbeing and reduce depressive symptoms by assisting participants to mobilise social support from family, friends and significant others.

The objectives of this trial are:
To proactively engage with students to hear their concerns in a non-judgmental manner and empathise with them.To reassure students about job loss/difficulty in finding a job and get them back to standard patterns of life, as early as possibleTo create a database of students who have either lost their jobs or are searching for jobs and linking them to the job market.To facilitate active linkage with various formal and informal resources to reduce their distress

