### Sample size and statistical analysis

A target sample size of 1440 participants (720 in each arm) with less than 5% loss to follow-up after 1 month of intervention is estimated to have 80% power. All participants will be included in the analysis according to their allocated group at randomisation. Statistical tests will use a *p*-value less than 0.05 for significance. All statistical analysis procedures will be done using STATA 14 and R version 3.6.3. Baseline summary statistics (mean, standard deviation, percentage) will be calculated based on groups. Chi-square tests and *T*-tests will be performed to test the significance of the study variables. The odds ratio of the outcome variables for the post-assessment will be calculated using logistic regression modelling and 95% confidence intervals. We will analyse descriptive summaries of socio-demographic aspects and the scores of WHO-5, PHQ-9 and MSPSS as the baseline and after 1 month.

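### Three unranked primary outcomes share a flat p<0.05 with no any-versus-all success rule; if any one suffices, the chance of a false significant primary result is about 11–14%, about half of it towards benefit

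*Protocol article*

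**What the plan says.** The abstract (Methods) names three primary outcomes without ranking them: "The primary outcomes of this study are mental wellbeing, depressive symptoms and perceived social support". The Outcomes section lists the same three with their instruments (WHO-5, PHQ-9, MSPSS-12), again unranked.

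Under Sample size and statistical analysis, one criterion covers statistical tests, a p-value "less than 0.05 for significance", and chi-square and t-"tests will be performed to test the significance of the study variables". Sidedness is not stated. The 1440 participants are said to give 80% power: the sample "is estimated to have 80% power". That figure is not tied to any of the three outcomes, so the sample size does not point to a lead outcome either.

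The hypothesis at the end of the Background is that befriended participants "will experience lesser symptoms of depression and have better mental health compared to participants who do not receive this intervention". It names depression and mental health, not social support. The abstract's Background and Discussion and the Aim section present mobilised social support as the means by which those two are to improve.

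**The concern.** The article fixes the number of primary outcomes and the threshold, but not what counts as success. Under the most permissive reading, one significant result out of three supports a claim that befriending works. The 5% then applies to each test and not to the trial's primary conclusion.

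The choice of outcomes adds to this. Perceived social support ranks equally with the two outcomes in the hypothesis, and the third phase of the intervention (Table 2) works directly on social support. MSPSS is therefore the outcome closest to what the callers do. A trial that moved MSPSS, but neither PHQ-9 nor WHO-5, could be reported as positive on a primary outcome although the hypothesis had not been borne out.

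**Working it through.** **Inputs from the protocol article**
- Three primary outcomes (abstract, Methods; Outcomes).
- Threshold 0.05 for each test (Sample size and statistical analysis).
- 12 agencies, six per arm, 120 participants each (Recruitment of clusters; Recruitment of participants).

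**Assumptions, because the article gives no figure**
- Two-sided tests.
- A common correlation r between the three test statistics, each oriented so that a higher value is better (PHQ-9 reversed). The range shown is 0 to 0.7.
- Any one significant primary suffices.

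**The plan's own figure.** The total checks: 12 × 120 = 1440. The 80% power cannot be reproduced, because no effect size, standard deviation, intracluster correlation or target outcome is given. No overall error rate is stated that could be compared.

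**Independent outcomes, no true effect**
- At least one significant result in either direction: 1 − 0.95³ = 1 − 0.857 = 0.143.
- At least one significant result towards benefit (0.025 in that tail for each test): 1 − 0.975³ = 1 − 0.927 = 0.073.
- One outcome alone: 5% in either direction, 2.5% towards benefit.

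**Correlated outcomes.** These rates come from simulation. The first pair of columns uses normal test statistics. The second pair uses a t-test on agency means, six against six, with 10 degrees of freedom, which is a valid cluster analysis.

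| r | Normal: either direction | Normal: benefit | Cluster means: either direction | Cluster means: benefit |
|---|---|---|---|---|
| 0 | 14.3% | 7.3% | 14.4% | 7.3% |
| 0.3 | 13.6% | 6.8% | 13.8% | 7.0% |
| 0.5 | 12.4% | 6.2% | 12.8% | 6.5% |
| 0.7 | 11.0% | 5.5% | 11.2% | 5.6% |

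A correct cluster analysis therefore leaves this inflation essentially unchanged.

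**Under alternative rules**
- 0.05/3 for each outcome (Bonferroni, which is also Holm's first step): 1 − (1 − 0.0167)³ = 4.9% in either direction if independent, and about 4% at r = 0.7.
- All three significant at 0.05: false benefit of at most about 0.4% when there is no effect on any outcome and r is at most 0.7. No split of alpha is needed.

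**Power at Holm's first step.** An outcome with 80% power at two-sided 0.05 has an expected z of 1.960 + 0.842 = 2.802.
- At 0.0167 the critical value is 2.394: Φ(2.802 − 2.394) = Φ(0.408) = 66%.
- At 0.025 the critical value is 2.241: Φ(2.802 − 2.241) = Φ(0.560) = 71%.
- With the 10-df cluster-level test, the same calculation from the noncentral t distribution gives about 61% and 68%.

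**The case against.** **An analysis plan may settle it.** Multiplicity is often handled in the full protocol or the SAP, neither of which is shown, and the 0.05 may be only a general convention. So one cannot infer that the trial has no multiplicity rule anywhere. What stands is narrower: this article itself states three unranked primaries and one flat threshold, and followed as written the two leave the success criterion undefined.

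**The hypothesis is worded jointly.** It expects less depression and better mental health together. If every primary had to succeed, there would be no inflation. This is a fair reading, but the article does not turn the wording into a decision rule, and the hypothesis does not mention the third primary. The article neither states nor excludes that one outcome is enough, so the figures here are conditional.

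**Direction.** A reader might take 11–14% as the chance of a false claim of benefit. It is not: it counts significant results in either direction, harm included. Under two-sided tests the benefit share is about half. A false-benefit rate of that order would require one-sided tests at 0.05 (14.3% at r = 0, 10.3% at r = 0.7), which the article does not state.

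**Neighbouring issues.** A reader might add the effect of testing without allowance for clustering. That is a separate matter, and its size depends on an intracluster correlation that the article does not give. The mention of anxiety and suicidal behaviour in the Aim, with no matching outcome, is likewise not a multiplicity question.

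**Conclusion.** The point holds in conditional form. With three unranked primaries at 0.05 each, and if any one suffices, the chance of at least one false significant primary result is about 14% for independent outcomes and about 11% at r = 0.7. Towards benefit it is about 7.3% to 5.5%, which is two to three times the 2.5% of a single two-sided test. The direction-specific figures assume two-sided tests, and the correlations are assumed throughout.

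The inflation is moderate. The gap in interpretation matters at least as much: the article allows a gain on perceived social support alone to be presented as primary success when neither depressive symptoms nor wellbeing has changed. This should be settled before outcome data are seen.

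**What to change.** State the success rule in the Outcomes section and the matching test rule in the statistical section. Any of three options would do:

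1. Keep three primaries and apply Holm: smallest p against 0.0167, the next against 0.025, the last against 0.05.
2. Keep PHQ-9 and WHO-5 as primaries under Holm (0.025, then 0.05) and make MSPSS a secondary outcome about mechanism. This follows the stated hypothesis most closely.
3. State that all primaries must be significant at 0.05, with no split of alpha.

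The text change is about two sentences; the real cost is power. Under Holm, an outcome with 80% power at 0.05 falls to about 66% (option 1) or 71% (option 2) at the first step, and somewhat lower with a 10-df cluster-level test. These are worst-case figures, because the later steps use larger thresholds. Option 3 costs power in another way: with 80% power for each of three independent outcomes, all three succeed with probability 0.8³ = 51%, and more often if they are positively correlated. Under any option, the 80% power statement should be restated for the chosen rule, naming the outcome or outcomes to which it applies.

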**Discussion:**

This trial will help assess whether participants who are offered emotional, social and practical support through befriending will experience lesser symptoms of depression and better mental health compared to participants who do not receive this intervention through mobilised social support from friends, family and others.

**Trial registration:**

Clinical Trial Registry India (ICMR-NIMS) CTRICTRI/2020/07/026834. Registered on 27 July 2020.

## Background

In India, the first case of COVID-19 was confirmed from the southern state of Kerala on 30 January 2020 [1]. On the 11th of March 2020, coronavirus disease (COVID-19) was declared a pandemic by the World Health Organization (WHO) [2]. Kerala declared a state-wide lockdown on the 23 March 2020 to prevent the community transmission of this virus [3]. As a result of the lockdown, people were forced to stay in their homes and faced with new realities of working from home, home schooling of children, temporary unemployment and lack of contact with other family members, friends and colleagues, which is likely to impact their mental and social health [4–7]. The unpredictability and uncertainty of controlling the disease and the misinformation around it will increase mental stress and concern among the people [4]. WHO defines mental health as a state of wellbeing in which an individual realises his or her own abilities, can cope with the everyday stresses of life, can work productively and can contribute to his or her community [8]. Recent studies have shown that even with a short-term lockdown, people report symptoms of mental stress and mental disorders like anxiety, depression, insomnia and post-traumatic stress disorder [5, 6]. The COVID-19 pandemic is likely to result in mental health problems varying from mild, time-limited distress to chronic, progressive and severely disabling conditions [9]. Findings from a recent online survey conducted among residents of New Delhi revealed that 55.3% of participants have sleep disturbances during the lockdown, 63.4% report work and income being severely affected, 7% report anxiety and restlessness and 12.1% felt helpless and depressed [10]. Thus, the pandemic is not just a threat to a country’s physical health but will also affect mental, social and economic well-being.

A survey by the Indian society of Labour economics showed job loss as the most severe immediate impact of COVID-19, while lower economic growth and rise in inequality as the probable long-term effects [11]. Loss of employment and the falling economy are expected to have a massive impact on mental health, especially those living under precarious conditions [12]. During such time, people experience fear, uncertainty, disruption, stress and other challenges that can trigger common mental health disorders like depression, anxiety and self-harm or suicidal behaviour [13–15].

The Ministry of Rural Development (MoRD), Government of India (GOI), launched an initiative in 2014 called the Deen Dayal Upadhyaya Grameen Kaushalya Yojana (DDU-GKY) to add diversity to the incomes of rural low-income families and to cater to the career aspirations of rural youth [16]. This initiative is present in 28 states of India and focuses on youth from poor rural families (aged 15 to 35 years). Currently, 1575 projects are being implemented by over 771 PIAs across India [16].

The Rajagiri College of Social Sciences, in Cochin, Kerala, is one of the PIAs, with 1500 students completing the course from 2016 till date, under the DDU-GKY initiative. This paper presents the study protocol of the REaCH (Resiliency Engagement and Care in Social Health) intervention trial. The ReaCH intervention trial involves using friendly and supportive telephonic interactions as an intervention for extending psychosocial support and creating a platform for sharing concerns of the youth, passed out from the DDU-GKY initiative, especially in the context of the COVID-19 pandemic and the associated lockdown.

People with socioeconomic vulnerability are more prone to common mental disorders like depression and anxiety [17–19], mainly due to isolation from inadequate social support and the absence of holistic health services [20]. Individuals from economically disadvantaged and vulnerable sections of society have been shown to appreciate and benefit from emotional and social support [21, 22]. One way of providing this support is through befriending, which has proven effective in improving mental health and reducing depression [21]. Befriending is defined as an intervention aimed at providing the client with additional social support by developing an empathic, non-judgmental, non-directive, affirming and purposeful relationship [21]. It involves a relationship between two individuals with regular input over a pre-specified period initiated and supervised by a third party [23]. Since the relationship is open-ended, it can develop over time from an artificial pairing of two people previously unknown to each other into a relationship in which the individuals are more comfortable sharing personal information [24]. Befriending is a non-directive emotional and social support typically administered by non-health professionals, and befriending conversations should avoid health-related matters and focus on enjoyable topics of interest to both parties [25].

In an epidemic outbreak, psychosocial interventions are essential [26] and social support has been shown to have a direct relationship with positive mental health and acts as a buffer against various stressors affecting mental health [27]. People with strong social relationships enjoy a sense of security and belonging to a network of systems that acts as a protective factor against various mental health issues [28].

Befriending is most often delivered by lay personnel or non-specialist workers, and [29] it is found that their use in the care of people with common mental disorders was cost-effective and cost-saving. In our trial, the intervention will be provided by DDU-GKY staff, which will enhance the existing staff, reduce cost, improve sustainability as the staff will be empowered to identify similar mental health issues in students in the future and increase acceptability as the staff are always available. Before the main trial, we plan a pilot trial among the students of the PIA at Rajagiri University, Kerala. Following the pilot trial, Rajagiri University team will lead the trial across 28 states of India, with the support of the Ministry of Rural Development. This nationwide telephonic befriending intervention is set out to address immediate priorities and strategies for providing emotional and practical support to the vulnerable people, in the context of COVID-19-related lockdown. We hypothesise that participants, whom we offer emotional, social and practical support through befriending, will experience lesser symptoms of depression and have better mental health compared to participants who do not receive this intervention.

## Methods

### Aim

The overall aim of the ReaCH intervention trial is to test the effectiveness of the befriending intervention among young adults in reducing mental health issues like anxiety, depression or suicidal behaviour in the context of the COVID-19 pandemic and the related restrictions. The befriending intervention will be used to determine if it can promote mental wellbeing and reduce depressive symptoms by assisting participants to mobilise social support from family, friends and significant others.

The objectives of this trial are:
To proactively engage with students to hear their concerns in a non-judgmental manner and empathise with them.To reassure students about job loss/difficulty in finding a job and get them back to standard patterns of life, as early as possibleTo create a database of students who have either lost their jobs or are searching for jobs and linking them to the job market.To facilitate active linkage with various formal and informal resources to reduce their distress

### Design

Cluster randomised controlled trial

### Outcomes

Mental wellbeing measured by World Health Organization-Five Well-being Index (WHO-5) [30, 31]Depressive symptoms measured by the Patient Health Questionnaire (PHQ-9) [32]Perceived social support measured by the Multidimensional Scale of Perceived Social Support (MSPSS-12) [33]

### Study location

The entire country of India, comprising 29 states, is further divided into six geographical zones and decided to include PIAs representing each zone, in consultation with the Director of National Institute for Rural Development and Panchayat Raj (NIRDPR), training head and her team. This clustering was done to capture the sociocultural and economic variations in settings and population and to address the needs specific to each zone. Table 1 lists the states that fall under each zone. 771 DDUGKY project-implementing agencies are functioning in India, spread across the different states in each of the zones. The number of PIAs within each state varies, 8 being the lowest and 160 being the highest. A list of PIAs in each zone will be prepared, and 12 PIAs will be randomly selected from each zone.

**Table 1 Tab1:** List of states that fall under each zone

Geographical zones	States in the zone
1. Northern zone	Delhi, Himachal Pradesh, Jammu and Kashmir, Punjab, Uttarakhand, Uttar Pradesh
2. North-East zone	Assam, Arunachal Pradesh, Manipur, Meghalaya, Mizoram, Nagaland, Sikkim, Tripura
3. Central zone	Madhya Pradesh, Chattisgarh
4. Eastern zone	Bihar, Jharkhand, Odisha, West Bengal
5. Western zone	Goa, Gujarat, Maharashtra
6. Southern zone	Andhra Pradesh, Karnataka, Kerala, Puducherry, Tamil Nadu, Telangana

### Recruitment of clusters (PIAs)

Two project-implementing agencies (PIA) will be recruited from each of the six zones (12 PIAs in total). For a PIA to be included in this study, it should be in one of the six zones and be an active, currently operational PIA with a full-time staff. A list of eligible PIAs will be prepared, and NIRDPR will use a computer-generated randomisation procedure to select the PIAs in the six zones. The NIRDPR will contact only those agencies meeting the inclusion criteria and invite them to participate in the study. This process will be continued till 12 consenting PIAs are selected for the project implementation. Six of the selected PIAs will be allocated to the intervention arm, and 6 PIAs will be allocated to the control arm. The state monitoring agencies will collect information on the number of full-time staff and contact details of students who completed their courses.

